### Assessments

Participants will be assessed at intake and at 10 points over the course of the study: before (T1), during (T2-4), and after the group-based phase (T5), after the subsequent 4-week follow-up waiting phase before individual CBT starts (T6), during (T7-9), and post the first four months of individual CBT (T10). Measures will include self-report questionnaires, interviews, observer-based ratings, EMA, experimental investigations, and analyses of hair steroids. Questionnaires will all be provided in paper pencil format and in German language. Interviews will be conducted face-to-face by intensively trained Master’s students majoring in clinical psychology who will closely be supervised by psychotherapists and psychotherapists in training for CBT, all of whom have Master’s degrees in clinical psychology. Participants will be provided with iPhones for the EMA. Over 7-day periods, time-contingent assessments will be taken 3 times per day and one hour after each of the three assessments. Participants will be given the chance to supplement time-contingent assessments with event-contingent assessments whenever they feel significantly distressed. Enrolled patients will also be asked to participate in an experimental investigation of ER skills and to provide hair probes. Participants will be compensated 50 Euros for the burden associated with study diagnostics, and an additional 20 Euros will be provided for participating in the experiment or providing hair probes. An overview of study variables, assessment points, and instruments is provided in Table 1.

**Table 1 T1:** Overview of study variables and instruments

**Domain**	**Instrument**	**T0**	**T1**	**T2**	**T3**	**T4**	**T5**	**T6**	**T7**	**T8**	**T9**	**T10**
Depressive symptom severity (primary outcome)	Hamilton rating scale for depression		✕		✕			✕				✕
Diagnostics	Structured clinical interview for DSM-IV Axis I, II	✕						✕				✕
Stressors	List of situational stressors		✕	✕	✕	✕	✕	✕	✕	✕	✕	✕
Additional indicators of mental health	Beck depression inventory II		✕	✕	✕	✕	✕	✕	✕	✕	✕	✕
	Scales of psychological well-being		✕	✕	✕	✕	✕	✕	✕	✕	✕	✕
	Pos. and neg. affect schedule		✕	✕	✕	✕	✕	✕	✕	✕	✕	✕
	Short scales of affective states relevant for psychotherapy		✕	✕	✕	✕	✕	✕	✕	✕	✕	✕
	SHARP/others		✕				✕	✕				✕
	Brief symptom inventory		✕				✕	✕				✕
	Depression anxiety and stress scale		✕	✕	✕	✕	✕	✕	✕	✕	✕	✕
Emotion regulation	Emotion reg. skills questionnaire		✕	✕	✕	✕	✕	✕	✕	✕	✕	✕
	ERSQ- others		✕				✕	✕				✕

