### Primary outcome

The level of depressive symptom severity as assessed by the Hamilton Rating Scale for Depression (HRSD) [42] will serve as the primary study outcome. The HRSD is a clinician-administered semi-structured interview that assesses symptoms of MDD. Based on patients’ responses, clinicians rate the degree of 24 symptoms such as depressed mood, feelings of guilt, sleeping disturbances, and anxiety on 3-point or 5-point Likert scales. Higher sum scores indicate greater symptom severity. The cut-off points of 10, 19, 27, and 35 represent thresholds for mild, moderate, severe, and very severe depression, respectively. The HRSD is sensitive to change and corresponds well with overall clinical ratings of severity [43,44].

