### Participants

Sample size for the group phase was set to *N* = 120 (*n* = 40 per condition). A minimum of *n* = 90 individuals (*n* = 30 per condition) is expected to complete individual CBT. Targeted sample sizes are based on power calculations. The intended sample of 120 individuals can be expected to provide sufficient power to detect small effects [67].

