### Statistical analyses

Data will be analyzed according to intent to treat and treatment completers principles. The intent to treatment analyses will be the primary level of analyses. Mixed effect modeling will serve as the main approach in the analyses of study data and in the treatment of missing values.

Growth curves of ER and depressive symptom severity will be computed per group on the basis of assessments before (T1-T5) and during individual CBT (T6-T10) to test for stand-alone and augmentation effects of ART. Slopes for the ART condition are hypothesized to be larger than those for the active or waitlist control groups, indicating the effectiveness of adaptive ER skills application enhancement and a decrease in depressive symptom severity by the ART program. In the secondary analyses, we will test for ART effects on well-being, positive, and negative affect. Bootstrapping enhanced, multilevel mediation analyses [68] will be conducted to test ER as a mediator of health improvements in the ART condition. Analyses will be conducted computing a total score of adaptive ER and separately for the different ART skills to understand the importance of specific ER skills. Moderated mediation analyses [69] will be used to examine the importance of specific ER skills in the mediation of positive health outcomes. Latent growth curve and latent change score modeling [70] will further be used in the investigation of reciprocal associations between levels and changes of ER and health outcomes. Comorbid symptom severity and potential confounding variables (i.e., general self-efficacy, perfectionism, and self-esteem) will be included in the analyses as moderating variables. The analyses of EMA and the experimental and biological data will serve to increase the validity of the ART evaluation. SEM-based Multi-Trait, Multi-Method approaches will be applied in the investigation of psychometric properties and in the comparison of outcomes by different assessment methods.

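### The group-phase HRSD effect is planned as a comparison of per-group slopes with no stated baseline adjustment; with a free intercept per arm this is a two-point change score, unbiased but less precise than an analysis adjusted for T1

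*Protocol article*

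**What the plan says.** The primary outcome is "The level of depressive symptom severity as assessed by the Hamilton Rating Scale for Depression (HRSD") (Primary outcome). Under Statistical analyses, mixed models are the main approach and "Growth curves of ER and depressive symptom severity will be computed per group", in two windows: T1 to T5 for the group phase and T6 to T10 for individual CBT. The hypothesis is that ART slopes are larger than those of either control arm. The group-phase effect is thus a between-arm difference in slope, and T1 is one of the modelled responses.

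The same section lists further variables that enter the analyses: comorbid symptom severity, self-efficacy, perfectionism and self-esteem, all as moderators. Baseline HRSD is not on the list, and no common T1 mean is mentioned. Neither is excluded.

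The Assessments section places the visits "before (T1), during (T2-4), and after the group-based phase (T5"). In Table 1 the row "Hamilton rating scale for depression" is marked at T1, T3, T6 and T10, while the BDI-II and the ERSQ are marked at every visit from T1 to T10. The Participants section states "Sample size for the group phase was set to *N* = 120 (*n* = 40 per condition").

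**The concern.** A slope through two points is the change between them divided by the elapsed time. Comparing such slopes with a separate intercept in each arm therefore compares mean change from T1 to T3. In a randomised trial the arms have the same expected T1 mean, so estimating a separate T1 mean for each arm spends information on a difference known to be zero in expectation. Using T1 as a covariate, or one T1 mean for all arms, removes that cost.

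What is at stake is precision on the primary outcome with 40 patients per arm. The article says "The intended sample of 120 individuals can be expected to provide sufficient power to detect small effects", which leaves little reason to give up precision that the existing T1 measurement already provides.

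**Working it through.** **Inputs from the article.** 40 per arm in the group phase; HRSD at T1 and T3 within T1 to T5; slope difference as the effect. The expected 30 completers per arm concern the individual CBT phase and are not used.

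**Inputs assumed.** The correlation r between T1 and follow-up HRSD, the ratio s of follow-up SD to baseline SD, and complete data at both visits. T1 is taken to be unaffected by allocation: the article puts it before the group phase but does not say in the text whether it precedes randomisation. For power only: two-sided 5% and an illustrative effect of 0.5 follow-up SDs.

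**The plan's own figure.** The article says "Targeted sample sizes are based on power calculations", but gives no alpha, power, r, SD or numeric effect, so N = 120 cannot be reproduced. The comparison below does not depend on how it was obtained.

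**Step 1, equal SDs (s = 1).** With common variance σ²:

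- variance of a change score: 2σ²(1 − r)
- variance after adjustment for T1: σ²(1 − r²)
- ratio, which is also the sample-size ratio: 2(1 − r)/(1 − r²) = 2/(1 + r)

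| Assumed r | Ratio | More patients needed | Total matching 120 adjusted | Power, change score | Power, adjusted |
|---|---|---|---|---|---|
| 0.3 | 2/1.3 = 1.538 | 54% | 185 | 0.47 | 0.65 |
| 0.5 | 2/1.5 = 1.333 | 33% | 160 | 0.61 | 0.73 |
| 0.7 | 2/1.7 = 1.176 | 18% | 141 | 0.82 | 0.88 |
| 0.8 | 2/1.8 = 1.111 | 11% | 133 | 0.94 | 0.96 |

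**Step 2, unequal SDs.** The ratio becomes (1 + s² − 2rs)/[s²(1 − r²)]. At s = 1.2, s² = 1.44:

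- r = 0.3: (2.44 − 0.72)/(1.44 × 0.91) = 1.72/1.3104 = 1.31, so 31% more
- r = 0.5: (2.44 − 1.20)/(1.44 × 0.75) = 1.24/1.08 = 1.15, so 15% more
- r = 0.7: (2.44 − 1.68)/(1.44 × 0.51) = 0.76/0.7344 = 1.03, so about 4% more (1.035 before rounding)

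The same ratio can be written 1 + (1 − rs)²/[s²(1 − r²)]. It is never below 1, so apart from the degree of freedom used by the covariate the change score cannot do better.

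**Step 3, where the loss comes from.** Generalised least-squares variances of the two-point slope difference, with a free intercept per arm against one common intercept, give the same ratios as steps 1 and 2. A common T1 mean therefore recovers the whole loss even though T1 stays among the responses.

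**Step 4, BDI-II and ERSQ.** These have five occasions in T1 to T5, so 2/(1 + r) does not carry over. Free against common intercepts cost 64% down to 10% more patients under compound symmetry with r from 0.3 to 0.8, and 12% to 36% under four illustrative random-slope structures. The gain exists, but its size depends on the covariance.

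**Step 5, T6 to T10.** The HRSD again has two points here, but T6 follows randomisation and the group phase. The arms need not have equal expected T6 means, so the argument behind steps 1 and 2 fails.

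**The case against.** The strongest reply is that the article does not state the model criticised here. The phrase about curves per group directly follows the sentence on mixed models, and a single group-by-time model with a common intercept fits it. Covariates and intercept constraints are often left to an analysis plan, and this is a condensed article. That part stands: the loss is conditional on free intercepts, and silence on the covariate would not be a finding by itself. But the article goes further than silence. It names the slope difference as the effect, puts T1 inside the curve, and schedules the primary outcome so that the slope has only two points. That is a definite choice with a better alternative.

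A second reply is that the size is unknown. This also stands. A reader might take a loss of 20% to 50% as a property of this trial; that range needs r of about 0.33 to 0.67 and equal SDs, and the documents support neither.

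Three further inferences should be resisted. T1 being a modelled response is not the fault; the free intercept is. The slope contrast is not biased: chance T1 imbalance and regression to the mean are the same loss of precision described another way, and not a second harm. And two HRSD points in each window do not make the ratio valid in both.

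Should the second group-phase HRSD mark in Table 1 belong to another visit in the window, there would still be two points, and the result would not change.

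**Conclusion.** The point holds as a conditional one about efficiency. If each arm has its own intercept, the group-phase HRSD contrast is a raw change score that a T1-adjusted or common-baseline analysis matches or beats. With equal SDs the cost runs from 54% more patients at r = 0.3 to 11% at r = 0.8; at a follow-up SD 1.2 times baseline it falls to between 31% and 4% for r from 0.3 to 0.7. All of these rest on assumed correlations and SDs. The documents do not support a claim of bias, a single figure for the loss, or any extension of these figures to the T6 to T10 slope, the BDI-II or the ERSQ. The change is worth making because it concerns the primary outcome and costs almost nothing.

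**What to change.** For the group-phase HRSD comparison, specify one mixed model across the three arms, with either T1 HRSD as a covariate or T1 means constrained equal across arms, and test the arm contrasts at the post-randomisation visits of that phase. State that T1 is measured before allocation, or at least cannot be affected by it.

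Apply the same common-baseline constraint to the BDI-II and ERSQ, without quoting the HRSD figures for them. Treat the T6 to T10 comparison separately, and do not enter T6 as if it were a baseline covariate.

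The cost is a change of wording in the analysis section. T1 HRSD is already scheduled. The covariate form uses one degree of freedom; the constrained form replaces three T1 means by one, and it also keeps patients whose T1 value is missing.

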Despite these encouraging findings, existing research on ART is limited by a number of factors. First, previous clinical studies used a short version of ART. Second, ART has not yet been compared with an untreated control condition or with a condition that accounts for unspecific therapeutic factors. Third, it has not yet been investigated whether ART would augment the effects of other empirically-evidenced treatments for MDD (possibly because enhanced ER skills might allow patients to engage more intensely in the therapeutic process, [31]). Finally, in previous study outcomes the effectiveness of ART was exclusively assessed through self-report measures and only at pre- and post-treatment.

In an attempt to clarify whether experimentally enhancing general ER skills reduces depressive symptom severity and whether fostering adaptive ER skills enhances the outcome of subsequent individual CBT for depression (iCBT-D), we will evaluate the efficacy of ART in a prospective randomized controlled trial. Stand-alone and augmenting effects of ART will be compared with a waitlist control condition and a condition controlling for active ingredients common to most empirically evidenced treatments. Primary (depressive symptom severity) and secondary outcomes will be assessed at intake and 10 points over the course of the study. Measurements will include self-reports, observer ratings, ecological momentary assessments (EMA) [32] and will include experimental investigations and the analysis of hair steroids in subsamples.

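### The mediation test is worded for the ART condition and names no randomised contrast as exposure, so it would not show that ART worked through emotion regulation; nor do the planned models rank the specific skills

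*Protocol article*

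**What the plan says.** All of the following is in the Statistical analyses section of the protocol article unless another section is named.

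- **Mediation:** "Bootstrapping enhanced, multilevel mediation analyses [68] will be conducted to test ER as a mediator of health improvements in the ART condition". The sentence names no treatment contrast.
- **Skills, one at a time:** "Analyses will be conducted computing a total score of adaptive ER and separately for the different ART skills".
- **Skills, second method:** "Moderated mediation analyses [69] will be used to examine the importance of specific ER skills in the mediation of positive health outcomes". The sentence names no moderator.
- **Moderators listed later in the section:** comorbid symptom severity and potential confounders ("i.e., general self-efficacy, perfectionism, and self-esteem) will be included in the analyses as moderating variables"). Treatment arm is not among them.
- **Between-arm comparison:** growth curves are planned for both ER and depressive severity, and "Slopes for the ART condition are hypothesized to be larger than those for the active or waitlist control groups".

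The Background gives the purpose as an "In an attempt to clarify whether experimentally enhancing general ER skills reduces depressive symptom severity". The Discussion says that the control conditions are there to remove the effects of time and of non-specific treatment factors.

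**The concern.** Within the ART arm, treatment does not vary. A mediation analysis confined to that arm can only take time, or each patient's own change, as its starting point. It then asks whether patients whose ER improved also became less depressed. Natural recovery, contact with a group, or a general lift in mood would produce the same pattern. CFT-C patients could show it too: the section on that treatment describes work on acceptance and problem solving, and acceptance is one of the competencies scored by the Emotion Regulation Skills Questionnaire (ERSQ).

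The Discussion criticises earlier ART studies for lacking an untreated control and a control for non-specific factors. A one-arm mediation analysis would bring that limitation back for the mechanism claim, although this trial has both controls.

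The skills question has a separate problem. Moderated mediation tests whether an indirect effect differs across levels of a third variable. It does not say which of several mediators carries the effect. Fitting each skill alone does not say so either, because each model omits the other, related skills and so partly credits their effect to the one in hand.

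**Working it through.** The article gives no effect size, power or error rate for mediation, so there is no planned figure to reproduce. The path sizes and correlations below are assumptions; the sample size is the article's.

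**1. Which planned analysis estimates which path**

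- ART to ER: between-arm ER slopes. Covered.
- ART to depression (total effect): between-arm depression slopes. Covered.
- ART to depression through ER, relative to a control: no sentence specifies it. The mediation sentence names no contrast, arm is not a listed moderator, and the latent change models concern reciprocal ER–outcome associations without reference to arm.

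**2. How often a one-arm association is significant when it has nothing to do with ART**

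Inputs: n = 40 per condition (Participants section); two-sided 5% level; assumed within-arm correlation r (absolute value) between ER change and symptom change, arising from causes other than ART. With Fisher's z, power ≈ Φ(atanh(r) × √(n − 3) − 1.96), and √37 = 6.083.

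| r | atanh(r) | × 6.083 | minus 1.96 | Significant |
|---|---|---|---|---|
| 0.2 | 0.203 | 1.23 | −0.73 | 23% |
| 0.3 | 0.310 | 1.88 | −0.08 | 47% |
| 0.4 | 0.424 | 2.58 | 0.62 | 73% |
| 0.5 | 0.549 | 3.34 | 1.38 | 92% |

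This is a simple correlation test standing in for the planned bootstrapped multilevel model, so it shows the order of size only.

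**3. A closer analogue by simulation**

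Settings: 40 patients per arm, five occasions (T1–T5), 1,000 runs per scenario, person-centred least squares, and a Monte Carlo 95% interval for the product of the two paths. ER rises by 0.5 between-person SD in the control arm over the phase. ART adds either 0 or 0.5 to that. Either ER has a causal coefficient of −0.4 on depression, or a shared mood state (loading 0.5) drives both and ER has no causal effect.

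| Scenario | ART arm only | Arm-by-time contrast |
|---|---|---|
| ART adds nothing to ER; shared state, no causal ER effect | 86% | 8% |
| ART adds nothing to ER; causal ER effect | 96% | 7% |
| ART adds 0.5 to ER; causal ER effect | 99.9% | 82% |
| ART adds 0.5 to ER; shared state, no causal ER effect | 99.7% | 62% |

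Entries are the share of runs that declare mediation. In the first two rows no indirect effect of ART relative to control exists. The one-arm analysis still declares mediation in 86–96% of runs, against 7–8% for the contrast. The third row shows the price in power. The fourth shows that the contrast is not a full cure: ER is not itself randomised, so a shared cause still yields 62%.

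**4. Separate tests of skills**

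The Emotion regulation section gives nine ERSQ competencies; the Background lists seven abilities. If each were tested at 5% and the tests were independent, the chance of at least one false positive would be 1 − 0.95⁹ = 37% for nine and 1 − 0.95⁷ = 30% for seven. Subscales of one questionnaire are likely to be positively correlated, which would lower these figures.

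**The case against.** The strongest reply is grammatical. The reference to the ART condition may describe the improvements to be explained rather than restrict the sample, in which case arm could be the predictor and all 120 patients would contribute. The neighbouring sentences do compare ART with both controls, and nothing says that control patients are left out. This stands as far as it goes. A reader might infer that the plan discards 80 of its 120 patients for the mechanism question; the text does not establish that. But the two readings answer different questions, and the article does not settle which is meant.

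Second, the controls do serve the mechanism question elsewhere. The ER slopes test between randomised arms whether ART raises ER, and if ART had no ER-specific effect, that comparison is where it should show. The laboratory experiment is also meant to inform causality. This too stands: it would be wrong to say that the trial cannot examine ER with its controls, or that its main aim fails. The slopes still do not give the indirect effect, and the experiment concerns instructed strategies and induced affect, not ART's effect on depression.

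Third, an article may leave exposure, timing and multiplicity to a fuller document. That would answer a complaint of silence. Here the article states a target for the mediation test and assigns a method to the skills question, and both can be judged as stated.

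Fourth, moderated mediation with arm as the moderator would contrast the arms. True, but arm is not among the moderators listed, and such a model still would not rank skills.

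**Conclusion.** The point holds as a specification that should be corrected. On its plain reading, the mediation analysis cannot separate ART from time or common factors; on the other reading it is ambiguous about its exposure. On either reading, the stated methods do not compare the specific skills.

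The size depends on assumptions that the article does not supply. The one-arm test is significant for reasons unrelated to ART in about 47% to 92% of trials for assumed correlations of 0.3 to 0.5, and in 23% at 0.2. The 92% should not be quoted alone. The simulated 86–96% likewise rests on assumed path sizes. The 30–37% for separate skill tests assumes independence.

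A reader might go on to infer that the trial's efficacy result is compromised. The document does not support that: the comparison of depression slopes between randomised arms is separate from the mediation analysis and is untouched. What is at risk is the claim that ART works through ER, and the claim that particular skills matter most.

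**What to change.** 1. **Exposure.** Define it as randomised arm, with ART vs CFT-C and ART vs waitlist as two named contrasts, and include all three arms.
2. **Time order.** Measure ER before the outcome. One option is ERSQ at T5 adjusted for T1 as mediator, with the Hamilton score at T6 adjusted for T1 as outcome. The other is to keep the multilevel repeated-measures model, with arm-by-time as exposure and lagged ER.
3. **Skills.** Enter them jointly as parallel mediators, with contrasts between their indirect effects and a multiplicity adjustment such as Holm's.
4. **Moderated mediation.** Keep it only for a moderator named in advance.
5. **Assumption.** State that the ER-to-outcome path assumes no unmeasured confounding, and add a sensitivity analysis.

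The cost is a rewording of analyses beyond the primary comparison. Table 1 schedules the ERSQ at T1 to T10 and the Hamilton scale at T1, T3, T6 and T10, so no assessment is added. There are two statistical costs. The arm contrast has less power than the one-arm test (82% against 99.9% in the simulated case with a true indirect effect), and entering correlated subscales together widens their intervals, so some skills may not be separable with 40 patients per arm.

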## Discussion

We should find support for our hypothesis that systematically enhancing general ER skills helps reduce depressive symptoms in individuals meeting criteria for MDD, given that deficits in ER are commonly considered a relevant risk and maintaining factor for this disorder. Former studies on ART, a program explicitly and exclusively focusing on an increase in adaptive ER skills application, have provided preliminary support for this assumption [8,19]. However, the validity of these studies has been compromised through a number of limitations such as the lack of an untreated control condition or a condition that controls for unspecific therapeutic factors, the lack of testing for augmentation effects of the ART on other treatments such as individual CBT for depression, and the exclusive use of self-reports at pre- and post-treatment. To improve on these limitations of previous studies and to advance the literature on associations between ER and MDD, we will systematically evaluate ART in a prospective randomized controlled trial.

This study will provide significant contributions to the literature. First, by controlling for time and unspecific treatment effects, the results will provide insight into the effects of enhancing the application of adaptive ER skills on symptoms of MDD. Second, from the two-phase design of this study that includes a period of individual CBT following the group phase, the stand-alone effects of ART on ER and depressive symptom severity can be tested, as well as the augmentation effects of ART on CBT outcomes. Third, the application of various measures, including self-reports, observer-based ratings, momentary assessments, experimental investigations, and the analysis of hair probes, will augment the reliability of findings and help to overcome methodological restrictions such as cognitive distortion and social desirability in retrospective testing and self-reports. The implementation of various assessment points over the course of the study will allow for detailed analyses of changes in and associations between ER and depressive symptom severity.

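### As worded, the mediation analysis concerns improvement within the ART arm, and no indirect effect of randomised arm through emotion regulation is stated; the sentence should define mediation on the ART-versus-control contrasts

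*Protocol article*

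**What the plan says.** In the protocol article, Statistical analyses, multilevel mediation models with bootstrapping "will be conducted to test ER as a mediator of health improvements in the ART condition". The surrounding text bears on how to read this:

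- Earlier in the same paragraph the same arm label is set against the controls: "Slopes for the ART condition are hypothesized to be larger than those for the active or waitlist control groups". That comparison covers both the candidate mediator and the outcome: "Growth curves of ER and depressive symptom severity will be computed per group".
- The next use of mediation concerns individual skills, not arms: "Moderated mediation analyses [69] will be used to examine the importance of specific ER skills in the mediation of positive health outcomes".
- Comorbid severity, self-efficacy, perfectionism and self-esteem "will be included in the analyses as moderating variables". Trial arm is not in that list.

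The Background gives the aim: "In an attempt to clarify whether experimentally enhancing general ER skills reduces depressive symptom severity". The Discussion gives the advantage claimed for the design: "by controlling for time and unspecific treatment effects, the results will provide insight into the effects of enhancing the application of adaptive ER skills".

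**The concern.** Within a single arm there is no treatment contrast. The only variable that can stand as the cause in a mediation path is time. Time carries whatever ART does, but also spontaneous recovery, regression to the mean and the non-specific effects of attending a group. From T6 it also carries individual CBT, which every arm receives. A significant path from time through ER to symptoms in ART patients therefore does not show that ART worked through ER.

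At stake is the mechanistic conclusion. The control arms exist to remove time and non-specific effects, and a mediation model confined to ART gives up that protection for the question of mechanism. It would also use one third of the randomised patients, although Table 1 schedules the ER questionnaire at T1 to T10 without restricting it to any arm.

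**Working it through.** The article gives no figure for the mediation analysis, so there is nothing to reproduce. The check has an algebraic part and a simulated part.

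**Inputs from the article.** 120 patients, 40 per condition (Participants). ER questionnaire (ERSQ) and BDI-II at every occasion T1 to T10; Hamilton scale at T1, T3, T6 and T10 only (Table 1). Share of patients in a within-ART model: 40/120 = 1/3.

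**Algebra.** Let c be the change in ER common to all arms, δ the extra change due to ART, and b the slope of symptoms on ER given time.

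- Within ART: indirect effect = (c + δ) × b.
- Randomised contrast: indirect effect = [(c + δ) − c] × b = δ × b.

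If ART adds nothing, δ = 0. The contrast then gives 0, while the within-ART model gives c × b. This is non-zero whenever there is common recovery (c ≠ 0) and any ER–symptom association (b ≠ 0), causal or not. If δ > 0, a share c/(c + δ) of the within-ART effect is still common change; with c = δ that share is half.

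**Simulation under no ART effect and no causal ER-to-symptom path.** 1,000 trials per setting, ART and one control arm of 40 each, five occasions (T1–T5), and a person-level percentile bootstrap with 800 draws. Assumptions not in the article: recovery 0 to 0.8 SD, ER–symptom correlation of size r from 0 to 0.5 arising from a shared cause, person-intercept SD 0.8, residual SD 0.6, random-slope SD 0.5 over T1–T5.

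Share of trials declaring mediation:

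| Recovery (SD) | r | Within ART | ART-versus-control contrast |
|---|---|---|---|
| 0.3 | 0.2 | 37.8% | 6.5% |
| 0.3 | 0.3 | 54.0% | 5.0% |
| 0.3 | 0.5 | 56.6% | 5.9% |
| 0.5 | 0.2 | 66.6% | 4.9% |
| 0.5 | 0.3 | 88.7% | 6.7% |
| 0.5 | 0.5 | 93.7% | 6.8% |
| 0.8 | 0.2 | 72.9% | 5.5% |
| 0.8 | 0.3 | 96.8% | 5.8% |
| 0.8 | 0.5 | 100% | 6.5% |

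Both ingredients are needed. With r = 0, the within-ART rate is 0.2% to 6.5% and the contrast 0.1% to 0.4%. With no recovery, both stay at or below about 6%.

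**Agreement of the two parts.** In this set-up b = −r, so the algebra predicts a within-ART effect of −(recovery × r): 0.3 × 0.2 = 0.06 (simulated mean −0.056), 0.5 × 0.3 = 0.15 (−0.143), 0.8 × 0.5 = 0.40 (−0.397).

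**Second simulation.** This one also assumed no ART effect. It used joint significance of the two paths instead of a bootstrap, recovery of 0.2 to 0.5 SD, residual correlations of −0.10 to −0.40, and 1,500 trials per setting. It gave 8% to 96% within ART and 2% to 6% with arm-by-time as the first path.

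**Limit of the match to the plan.** Five waves between T1 and T5 fit BDI-II. The Hamilton scale has only two values in that window (T1 and T3), so these rates should not be read as rates for the primary outcome.

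**The case against.** A reader might infer that the plan deliberately excludes the control arms from the mediation analysis. The article does not say so. The phrase could be loose wording for improvements caused by ART, with arm as the independent variable. The context gives that reading some support, since the preceding sentences compare arms and test ART effects. The method is given by a reference, and a condensed article may leave the model's paths and covariates to a fuller document. This stands: what can be criticised is the sentence as worded, not a proven intention. It does not dispose of the point. The contrast that defines the mediated effect is part of the question asked, and the published sentence states one rather than leaving it open.

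A second objection is that the planned slope comparisons protect against the error: if all arms recover equally, ART should usually show no advantage on ER or depression, and a claimed ART mechanism would contradict the trial's own main result. This is a real but partial safeguard. The mediation is not made conditional on those comparisons. Even when ART slopes are steeper, the within-ART effect still mixes common with ART-specific change, and it cannot separate ART versus waitlist from ART versus CFT-C.

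Third, a reader might infer that ordinary recovery by itself creates spurious mediation. It does not, as the r = 0 rows show. A non-causal ER–symptom association is also required. That is plausible here, because the Background reports that ER deficits are linked to depressive symptoms, and ERSQ and BDI-II are self-reports taken at the same occasions. Its size is still an assumption.

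Finally, the randomised contrast does not settle causality either. The path from ER to symptoms is not randomised. If ART lowered symptoms by another route and ER followed mood, a between-arm model could still suggest mediation. The simulations cover only the case in which ART adds nothing.

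**Conclusion.** The point holds for the sentence as written. Read literally, it defines mediation within the ART arm, and no between-arm indirect effect is stated anywhere in the article. Carried out that way, the analysis could declare an ER mechanism in roughly 40% to 100% of trials in which ART adds nothing, against about 5% to 7% on the randomised contrast. This range rests on assumed common recovery of 0.3 to 0.8 SD and an assumed non-causal correlation of 0.2 to 0.5; without either ingredient the excess disappears.

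The consequence is confined to a secondary, mechanistic analysis. It would be wrong to infer that the primary Hamilton comparison is compromised, or that the trial never compares ER between arms, since it plans to do so. The sentence should be corrected because the mechanistic claim depends on it. If a between-arm model was always intended, the correction is only a clarification.

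**What to change.** Reword the mediation sentence along these lines: ER will be tested as a mediator of the effect of randomised arm (ART versus waitlist and ART versus CFT-C) in all randomised patients, with arm, or arm-by-time, on ER as the first path, adjusting for T1 ER and T1 symptoms. Any model within ART alone will be descriptive.

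Add one sentence stating that the ER-to-symptom path remains non-randomised.

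Where possible, use the time order already in Table 1: for example, ERSQ change from T1 to T5 before the Hamilton score at T6 for the stand-alone question, and ERSQ up to T6 before the Hamilton score at T10 for augmentation. This is desirable; the definition by randomised arm is the essential change.

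The cost is a few lines of analysis wording. Table 1 already schedules the measures without restriction by arm. The downside is that some apparent within-arm mediation may no longer be significant.
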